##### Exclusion criteria

Patients who meet any of the following criteria will be excluded: (1) claustrophobic or other fMRI scanning contraindications; (2) unable to understand or record in the urticaria diary; (3) pregnant or lactating; (4) severe primary diseases, such as cardiovascular, liver, kidney, digestive, or hematopoietic conditions; (5) progressive malignant tumors or other severe wasting diseases that increase the risk of concurrent infection and bleeding; (6) unconscious, unable to express subjective symptoms independently, or diagnosed with a psychiatric illness; (7) and patients who have participated in similar research within the past month.

#### Healthy controls

##### Inclusion criteria

Participants who meet all of the following criteria will be included in this study: (1) have not participated in similar research within 1 month; (2) right-handedness of either sex; between the ages of 18 and 70 years, with a minimum of 6 years of education; (3) no history of urticaria or other allergic diseases; (4) no drug use for at least 15 days before entering the study; (5) no metal implants, no fMRI scanning contraindications; (6) all physiological indexes are common, no functional or organic diseases; (7) No participation in similar or other clinical studies; (8) volunteer for this study and provide signed informed consent.

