## Introduction

Chronic urticaria (CU) is a skin disease characterized by reddish wheals and unbearable itching, with or without angioedema, lasting for ≥6 weeks. Chronic spontaneous urticaria (CSU) is the most common type of CU (71.2%) and is characterized by urticaria symptoms without inducing factors (1, 2). The prevalence of CU is particularly high within the Asian population (1.5%), with a higher prevalence among women than men (3). Owing to complicated conditions, recurrent symptoms, and few effective curative treatments, patients are often required to take high-cost drugs for an extended period. This significantly impacts their quality of life and places a considerable burden on both individuals and society (4, 5).

The latest clinical guidelines for urticaria state that modern second-generation H1-antihistamines should be employed as first-line treatment drugs (2). Despite this, the guidelines do not provide specific recommendations for individual specific drugs due to insufficient research on the effectiveness and safety evaluation of all second-generation H1-antihistamines. Furthermore, the guidelines recommend using omalizumab or cyclosporine for patients who have an inadequate response to second-generation H1-antihistamines. However, there are still some patients who do not benefit from these medications (6, 7). The Taiwanese Dermatological Association consensus proposes that non-pharmacological therapies are also an important approach in alleviating urticaria (8). As an nondrug alternative therapy, acupuncture has been widely used to treat pruritic dermatoses, including CSU, and has demonstrated curative effects (9, 10). However, due to a lack of high-quality evidence supporting its use and insufficient elucidation on the mechanisms underlying acupuncture’s effects, recent clinical practice guidelines do not recommend or report the beneficial effect of acupuncture on CSU (11, 12). Therefore, further research is needed to provide additional evidence.

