## Methods and analysis

### Study design

This is a parallel randomized sham-controlled functional neuroimaging study. Fifty CSU patients and 25 matched healthy subjects will be randomly assigned to the verum or sham acupuncture groups at a 1:1 ratio. The total observation period of this study is 6 weeks, including a baseline period of 2 weeks and a clinical treatment period of 4 weeks. Before treatment, all participants (*n* = 75) will undergo clinical index evaluation, magnetic resonance scanning, and microflora collection. Following treatment, only the CSU patients will be reassessed for these indicators. The study flow chart is presented in Figure 1, and the schedule of enrolment, interventions, and assessments is shown in Table 1. This trial will be reported following the Standard Protocol Items: Recommendations for Interventional Trials (SPIRIT).

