##### Inclusion criteria

The study will enroll patients who meet the following criteria (1) meet the diagnostic criteria of CSU as defined in “The international EAACI/GA^2^LEN/EuroGuiDerm/APAAACI guideline for the definition, classification, diagnosis, and management of urticaria” (2); (2) right-handedness of either sex, aged between 18 and 70 years, with a minimum of 6 years of education; (3) urticaria activity score 7 (UAS7) > 14; (4) no metal implants, no fMRI scanning contraindications; (5) patients who have not taken any antihistamines within 2 weeks before entering the study, and have not used steroid hormones or immunosuppressants within the last month; (6) no acupuncture treatment within 3 months before entering the study, no participation in other ongoing clinical studies; (7) and patient who have provided signed informed consent and volunteered to participate in this study.

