### Sample size

Due to the particularity of the neuroimaging mechanism, the clinical sample calculation method is not applicable. According to fMRI sample size research, each group should include at least 6–12 patients (40), while the statistical data of 20 subjects resembles that of large sample data for 130 subjects (41). Considering the uncertain factors in this study, including the loss or elimination of subjects and unavailable data due to head movements, we included 50 patients and 25 matched healthy persons in this study.

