### Statistical analysis

#### Clinical data analysis

All baseline and clinical response index data will be analyzed using the SPSS software (version 22.0). Measurement data will be expressed as mean ± SD. Following the normality test, an independent samples *t*-test will be used if the criteria of normal distribution and homogeneity of variance are met. Otherwise, a non-parametric test (Mann–Whitney U-test) will be used. Count data will be analyzed by the two-sided χ^2^ test. A *p* < 0.05 will be considered significant.

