#### Microbiota analysis

Clinical skin and intestinal flora DNA will be analyzed using 16S rDNA amplicon sequencing to determine the microbial composition of the samples. 16S rRNA gene sequencing will be performed using Novogene (Beijing, China), according to the manufacturer’s instructions. Raw data obtained by sequencing will then be spliced and filtered to obtain clean data. The DADA2 method will be employed to reduce noise based on the effective data, and sequences with abundances <5 will be filtered out to obtain the final amplicon sequence variants (ASVs).

For the ASVs obtained, species annotation will be performed on representative sequences to obtain the corresponding species information and abundance distribution. Simultaneously, the abundance, alpha diversity calculation, Venn diagrams, and petaline graphs of ASVs will be analyzed to obtain species richness and evenness information. Additionally, multiple sequence alignment of ASVs will be carried out to construct a phylogenetic tree. Principal coordinate analysis (PCoA), principal component analysis (PCA), nonmetric multi-dimensional scaling (NMDS), other dimension reduction analysis, and sample phylogenetic tree display will be applied to explore the differences in community structure between CSU patients and healthy people, and between the acupuncture group and sham acupuncture group. To further explore the community structure differences among grouped samples, statistical analysis methods, including *t*-test, MetaStat, and LEfSe, will be employed to test the significance of species composition and community structure of grouped samples.

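### The CSU-versus-healthy comparison is not randomised, and none of the tests named for it adjusts for age or sex, so an imbalance could be reported as a feature of the disease

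*Protocol article*

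**What the plan says.** - **Matching.** Study design describes "Fifty CSU patients and 25 matched healthy subjects", and Sample size repeats the description: "we included 50 patients and 25 matched healthy persons in this study". Neither names a matching factor.
- **Control entry.** The healthy-control inclusion criteria require "right-handedness of either sex; between the ages of 18 and 70 years, with a minimum of 6 years of education". The patient criteria set the same limits: "right-handedness of either sex, aged between 18 and 70 years, with a minimum of 6 years of education".
- **Sex distribution.** The Introduction says that chronic urticaria occurs "with a higher prevalence among women than men". It gives no proportion.
- **Microbiota.** The Microbiota analysis section lists patients against healthy people as a comparison of interest, alongside acupuncture against sham. It states that "statistical analysis methods, including *t*-test, MetaStat, and LEfSe, will be employed to test the significance of species composition". No age or sex covariate is mentioned.
- **Clinical and baseline data.** The Clinical data analysis section states that "an independent samples *t*-test will be used if the criteria of normal distribution and homogeneity of variance are met", with Mann-Whitney as the alternative. Study design has all 75 participants assessed before treatment.
- **fMRI.** Covariate regression appears once, as the last preprocessing step, and the covariates are not named. The connectivity sections describe how maps and dynamic measures are built and thresholded. They name no test between groups.

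**The concern.** Being a patient or a healthy control cannot be randomised, so nothing in the design balances this contrast unless matching or adjustment does. Sharing an age range of 52 years, with both sexes eligible, sets who may enter. It does not make the two groups alike within that range. The article itself gives a reason to expect more women among the patients.

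The contrast carries one of the study's stated aims, which is to describe the brain-network and microbiota features of CSU (Introduction and Discussion). If an outcome varies with age or sex, and the groups differ in age or sex, a plain two-group test attributes the difference to disease. Even controls who are matched well on average are better analysed with the matching factors in the model, and the named tests leave them out.

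**Working it through.** The article gives no effect size, SD or power to reproduce. The only figure that can be checked is the total: 50 + 25 = 75, which agrees.

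**Inputs from the article:** 50 patients, 25 controls, significance at p < 0.05. Two-sided testing is assumed for the t-test, because the article says so only for the χ² test.

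**Inputs assumed, because the article gives none:** the difference in mean age (in SD), the correlation r of a feature with age, the difference in the share of women, and the effect of sex on a feature (in SD). If the SD of age were 14 years, also an assumption, a gap of 0.5 to 0.75 SD would be 7 to 10.5 years.

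**Step 1. Standard error of a standardised difference:**
√(1/50 + 1/25) = √0.06 = 0.245, with 50 + 25 − 2 = 73 degrees of freedom.

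**Step 2. Spurious difference when disease has no effect:**
from age, d = r × age gap; from sex, d = sex effect × difference in share of women.

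**Step 3. False-positive rate:** rejection probability of the two-sided 5% t-test from the noncentral t, with noncentrality d / 0.245.

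| Source | Assumption | d (SD) | d / 0.245 | False-positive rate |
|---|---|---|---|---|
| Age | gap 0.25, r 0.2 | 0.05 | 0.20 | 5.5% |
| Age | gap 0.5, r 0.3 | 0.15 | 0.61 | 9.3% |
| Age | gap 0.5, r 0.4 | 0.20 | 0.82 | 12.7% |
| Age | gap 0.75, r 0.3 | 0.225 | 0.92 | 14.8% |
| Age | gap 0.75, r 0.4 | 0.30 | 1.22 | 22.7% |
| Sex | 20 points, effect 0.5 | 0.10 | 0.41 | 6.9% |
| Sex | 30 points, effect 0.8 | 0.24 | 0.98 | 16.2% |

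Outside this range the rate can be lower (gap 0.25, r 0.1: 5.1%) or much higher (gap 1.0, r 0.5: 52.2%). The conclusion does not rest on either extreme.

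**Step 4. Does adjustment work?** A simulation of 8,000 runs per scenario, with no disease effect and a linear age effect, compared the plain test with a model that also contains age:

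| r, age gap | Unadjusted | Age in model |
|---|---|---|
| 0.3, 0.5 SD | 9.6% | 5.1% |
| 0.3, 1.0 SD | 22.6% | 4.9% |
| 0.5, 0.5 SD | 17.5% | 5.1% |
| 0.5, 1.0 SD | 52.3% | 5.0% |

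The unadjusted column agrees with the noncentral t values for the same four cases (9.3%, 22.7%, 17.2%, 52.2%). Adjustment returns the rate to nominal in each. The simulation used age alone; sex and education were not simulated.

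**The case against.** The strongest reply is that this is a condensed article. It says twice that the controls are matched, and nothing in it says otherwise. Eligibility lists define who may enter and rarely say how controls are chosen against enrolled patients. The matching factors and group-level covariates may stand in the full protocol or the analysis plan. The microbiota list is worded as open, the sizes above are all assumed, and the primary outcome and the randomised comparison are not touched.

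Much of this stands, and it rules out several stronger readings that a reader might infer:

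- **That no matching is done.** Silence about the factors does not show this.
- **That 25 against 50 rules out matching.** It rules out one control per patient. One control per two patients fits exactly, since 2 × 25 = 50.
- **That the groups share nothing but an age band.** Right-handedness and minimum education are common to both, and control skin is sampled at sites corresponding to the patients' wheals. None of these balances age or sex.
- **That the brain results rest on a stated unadjusted test.** No fMRI group test is stated, and nothing excludes covariates in SPM12. Equally, the covariate regression in preprocessing should not be taken for adjustment of a group comparison.

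What the reply does not answer is the choice that the article does make. It names specific tests for the microbiota comparison of patients with healthy people, and a plain t-test or Mann-Whitney test for baseline data, none with an age or sex covariate. An unstated matching procedure would not put the matching factors into those tests.

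**Conclusion.** The point holds as a fault in a stated analysis choice for a non-randomised contrast. It is clearest for the microbiota, where the comparison and its tests are both written down. It extends to baseline clinical measures if the named tests are used to compare patients with controls. For fMRI it is only a request that the group-level model name its covariates.

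The size depends wholly on assumed imbalances. Per feature, the false-positive rate runs from about 5.5%, which would not matter, to about 23%, which would. The article has no figures to say where in that range the study will fall, and good matching on age and sex would put it near the lower end. The case for acting is that the risk is plausible, the remedy is nearly free, and in the simulated scenarios it restored the nominal rate. The randomised acupuncture-versus-sham comparison is unaffected.

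**What to change.** - **Microbiota.** For patients versus healthy people, replace the plain t-test on diversity and taxa with models containing group, age, sex and years of education. Where MetaStat or LEfSe is kept, report it beside the adjusted result.
- **Baseline clinical measures.** Use the same model wherever patients are compared with controls.
- **fMRI.** Name the same covariates in the SPM12 group-level model for rsFC and dFC.
- **Matching.** State the factors on which controls are matched and include them in these models. Recruiting controls to sex and age bands is optional; the point does not depend on it.

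**Cost.** Three covariates take the residual degrees of freedom from 73 to 70, with slightly more analysis work. Age, sex and education are already checked at eligibility. Education should be recorded in years, not only as meeting the minimum. The adjustment remains available even if recruitment is complete.

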Recent studies on brain networks have shown that DMN largely overlaps with acupuncture response areas (26, 27). That is, verum acupuncture can regulate the DMN and increase the functional connectivity of the DMN with the sensorimotor network, pain emotion, and memory-related brain regions. Moreover, acupuncture can exert therapeutic effects by modulating microbiota (28, 29). These underlying mechanisms also play a crucial role in both the development and resolution of CSU. Accordingly, we have designed a randomized sham acupuncture-controlled trial. fMRI will serve as the primary research method while the key DMN brain regions regulated by acupuncture for CSU treatment will represent the seed points. Furthermore, we plan to analyze the microbiota and clinical indicators. The primary objective of this study is thus to systematically elucidate the brain network mechanism associated with the treatment of CSU by acupuncture. Our goal is to provide robust scientific evidence to support the clinical application of acupuncture as a treatment modality for CSU.

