##### Exclusion criteria

Participants who meet any of the following criteria will be excluded: (1) CSU disease history or allergic constitution; (2) pregnant or lactating; (3) Hamilton anxiety scale score (HAMA) > 7 or Hamilton depression scale score (HAMD) > 7; (4) metal implants, fMRI examination contraindications like claustrophobia; (5) severe asymmetry of skull anatomical structure or apparent lesions detected while scanning; (6) unconscious or unable to express subjective symptoms independently.

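### Healthy controls have no limit on recent acupuncture although patients must be free of it for 3 months, so recently needled controls could enter the baseline CSU-versus-healthy comparison; the likely effect is small and the remedy cheap

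*Protocol article*

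**What the plan says.** Inclusion criterion (6) for CSU patients requires "no acupuncture treatment within 3 months before entering the study".

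The healthy-control lists are itemised separately, with eight inclusion and six exclusion items. The items that bear on prior exposure or health are:

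- Inclusion (1): "have not participated in similar research within 1 month". Item (7) adds a bar on taking part in similar or other clinical studies.
- Inclusion (4): "no drug use for at least 15 days before entering the study".
- Inclusion (6): "all physiological indexes are common, no functional or organic diseases".
- Exclusion (1): "CSU disease history or allergic constitution". Exclusion (3) removes anyone scoring above 7 on HAMA or HAMD.

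None of the fourteen items mentions acupuncture.

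On what acupuncture does, the Introduction says that "verum acupuncture can regulate the DMN and increase the functional connectivity of the DMN" with several other networks and regions, and that "acupuncture can exert therapeutic effects by modulating microbiota". Under Study design, all 75 participants have MRI and microbiota sampling before treatment, and only patients are measured again. Microbiota analysis plans to examine "differences in community structure between CSU patients and healthy people". The Discussion aims to describe the pathological features of brain networks in CSU.

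**The concern.** The controls serve as the healthy reference at baseline. Patients cannot bring recent acupuncture into that comparison, but controls can. The exposure is the trial's own treatment, and the Introduction names the two domains being compared, brain connectivity and microbiota, as things it can change. Any residual effect would therefore sit on one side only and act as a systematic difference between the groups rather than as noise common to both.

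At stake is how far the baseline CSU-versus-healthy findings can be read as features of the disease. Because controls are measured only once, no later measurement would reveal the problem.

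**Working it through.** **Do the other control criteria close the gap?**

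| Control criterion | Does it exclude recent acupuncture? |
|---|---|
| No drugs for 15 days | No; acupuncture is not a drug |
| No similar research within 1 month; no similar or other clinical studies | Only acupuncture received within a study, not ordinary care or use for wellbeing |
| Normal indexes, no functional or organic disease | Makes it less likely; describes status at entry, not past treatment |
| No CSU or allergic history; HAMA and HAMD not above 7 | Makes it less likely; does not exclude it |

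A volunteer needled shortly before entry for a complaint that has since resolved could meet every item. Condensation of the protocol into an article is a weak explanation, because both lists are itemised and the control list states its own exposure limits.

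**Is the comparison planned?** For microbiota it is explicit (Microbiota analysis). For fMRI it is inferred: controls are scanned once, at baseline (Study design), and the stated aim is to describe pathological network features (Discussion). The article gives the control scans no other evident use.

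**How large could the bias be?** The plan has no figure to reproduce, since Sample size gives no formula-based calculation.

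Inputs:

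- From the Sample size section: 50 patients and 25 controls.
- Assumed, because the documents give neither: k = 1 to 5 controls exposed (4% to 20%), each with a residual effect d = 0.3 to 0.8 SD.

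Formulas, for one continuous measure with common SD:

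- Standard error of the difference = √(1/50 + 1/25) = √0.06 = 0.245 SD.
- Shift in the control mean = (k/25) × d.
- False-positive rate of a two-sided 5% test when there is no true difference = P(Z > 1.96 − δ) + P(Z < −1.96 − δ), where δ = shift/0.245.

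| k | d (SD) | Shift (SD) | δ | False-positive rate |
|---|---|---|---|---|
| 1 | 0.3 | 0.012 | 0.05 | 5.0% |
| 2 | 0.5 | 0.040 | 0.16 | 5.3% |
| 5 | 0.3 | 0.060 | 0.24 | 5.7% |
| 5 | 0.8 | 0.160 | 0.65 | 10.0% |

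Even the extreme case is below one standard error. With one or two exposed controls and a residual effect of 0.3 to 0.5 SD, the test is almost unchanged.

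**The case against.** The strongest case on the other side has four parts.

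1. **The protocol does not say why patients have the washout.** They enter a sham-controlled trial that depends on patient blinding, and recent needling could undermine the sham or carry over to UAS7. Neither reason applies to people measured once and not treated. This stands: different rules for different roles are not in themselves a contradiction. What remains is that the controls' own role, as a reference for connectivity and microbiota, gives a separate reason to restrict the exposure.

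2. **The Introduction is silent on persistence.** It does not say that the changes last for weeks or months, or that they occur in healthy people. This also stands. The bias needs a residual effect that the documents do not assert, which is why d is only an assumption. A reader might infer that patients would look more deficient in connectivity than they are. The documents do not support a direction, for connectivity or for microbiota.

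3. **The controls are already screened for good health,** which removes many ordinary reasons for seeking acupuncture. This makes the upper end of the assumed exposure unlikely, but it does not exclude exposure.

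4. **Other unlisted exposures, such as diet, could also matter.** That is true. Acupuncture differs in that the plan already restricts it for one side of the comparison and itself names it as acting on these measures.

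A single 5% test is also a poor stand-in for thresholded whole-brain maps or LEfSe, so the rates above show scale only.

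**Conclusion.** The asymmetry is in the text and touches a planned comparison. It is a minor design gap. Under the assumed inputs the bias is 0.01 to 0.16 SD against a standard error of 0.245 SD, and it is negligible over much of that range. The documents fix neither its size nor its direction.

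A reader might go further and infer that the CSU-versus-healthy contrast defines the DMN dysfunction that treatment is meant to correct, so that contaminated controls would misdirect the whole study. The text does not support this. Region of interest fixes five seed regions with coordinates from the group's previous work, and the Introduction treats DMN dysfunction in CSU as already established. Nor is the UAS7 primary outcome or the randomised verum-versus-sham contrast affected. That last statement takes Randomization and blinding and Interventions as governing, where only patients are allocated and treated. The wording in Study design that also assigns healthy subjects is a separate inconsistency.

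**What to change.** Add to the healthy-control inclusion criteria the condition that patients already meet: no acupuncture in the 3 months before entry. This takes one line and one screening question, and may turn away a few volunteers.

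If controls are already enrolled, ask each about acupuncture in that period, record the answer, and repeat the CSU-versus-healthy imaging and microbiota contrasts without those exposed, as a sensitivity analysis. The cost is a slightly smaller control group there. With 5 of 25 removed, for example, the standard error rises from 0.245 to √(1/50 + 1/20) = 0.265 SD. Prior acupuncture recalled after enrolment is also less certain than a screening criterion applied beforehand.
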